### Data monitoring

An independent Data Monitoring and Safety Committee (DMC) has been formed, consisting of an expert statistician uninvolved with the trial, and a researcher in the field who is also an experienced physiotherapist, uninvolved with the trial. The role of the DMC is to monitor the data from the trial and to make recommendations to the Chief Investigator and trial manager and to consider any safety issues for the trial. The DMC is independent from the sponsor and competing interests. Meetings will be held during recruitment, and then when recruitment reaches *n* ≥ 50. The trial team will prepare the following reports for that meeting:

Recruitment reportDemographics of participantsNumber of participants completed, number of participants to follow-up, number of participants lost to follow-upNumber of participant ARAT (primary outcome) assessments performed at baseline, 6 weeks and 6 monthsAdverse eventsAdherence data.

Following the meetings, a report will be provided to the Chief Investigator, by the chair of the DMC, and the Chief Investigator will report the findings to the Trial Management Committee. When the participant number exceeds 50, a report will be provided for the next DMC meeting of the outcome data, unblinded, by the trial statistician. At meetings where the unblinded outcome data is discussed, there will be both an open and a closed meeting, with the closed meeting including the DMC, the trial manager, and trial statistician if required (and not the Chief Investigator).

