## Methods and analysis

### Trial design

This study is a two-arm, assessor-blinded, multicentre randomised controlled trial comparing task-specific treatment to usual care for the arm and hand after stroke. The study will occur in participants’ homes with the interventions delivered by therapists upskilled and employed to deliver the task specific research intervention.

Research personnel responsible for data collection will be blinded to the treatment group to which a participant is assigned. Those involved in the delivery of the treatment will not be blinded. We have also aimed to blind participants as much as possible to group allocation by (a) not informing them deliberately of group allocation – instead they were told they would be visited by a therapist soon and the approximate timeline of this visit. The visit would occur within a week of assessment (if allocated to the task-specific treatment) or in approximately 6 weeks (if allocated to usual care).

The trial is registered with the ANZCTR. Appendix 1 shows key Trial Registration data.

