### Study methods

Participants will be stratified according to severity of upper limb impairment, and state (NSW, and Victoria) using randomised permuted blocks (block sizes 4 and 6) in a 1:1 ratio. Baseline severity of upper limb impairment will be categorized using scores on the ARAT (subgroups defined by Morris et al. (43) (Group 1: score 0–3; Group 2 score 4–28; Group 3 score 29–57)). Randomisation will occur after baseline assessment using a computer-generated random allocation sequence, created by the Data Sciences unit at the HMRI. The Trial Manager will randomise each participant using REDCap, then inform the therapist of the treatment allocation and book assessment appointments.

Outcome assessors will be blinded to the treatment group to which a participant is assigned. Owing to the nature of this behavioural intervention, therapists delivering treatment cannot be blinded. Participants will be instructed in their treatment but will be blinded to the treatment group.

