### Data management

The end of the trial for an individual participant is defined as completion of the 6-month follow-up. The definition of the end of the trial as a whole is the date when all participants have completed their final assessment at follow-up or have been lost to follow-up.

The Trial Manager/research assistant at each site will enter data into REDCap. The Data Sciences unit at HMRI will develop and upload the randomisation schema; develop and maintain the data management system; develop a data management plan for the data; prepare and clean the data for analysis; write the statistical analysis plan and conduct the statistical analysis.

The Trial Manager/research assistant will collect information about the number of eligible participants approached, recruit the participants, including obtaining consent from those who choose to join the study and will ‘track’ each participant to ensure data collection at the designated times.

Study staff will review of data for accuracy during data entry, with data quality aided by logging of data entry and changes (with comments). The Trial Manager/research assistant will also be responsible for the secure storage of data coming from participants across research sites. Paper records of assessment scores and questionnaires will be anonymised using code identifier and kept in a locked filing cabinet in an office that is locked when not occupied by the research team.

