### Statistical analysis

Intention-to-treat (ITT) and per protocol (PP) analyses will be conducted. The ITT population will include all subjects who are randomised whereas the PP population will include those subjects who received 90% allocated treatment. The primary outcome measure (ARAT at the end of intervention at 6 weeks) will be analysed using analysis of covariance fitted within a Generalised Linear Mixed Model (GLMM) framework to adjust for the repeated measurements on individuals. The outcome in the model will be the individual’s ARAT (immediately after 6 weeks of intervention/6 months after intervention commencement); fixed effects in the model will be group, time and the interaction of time by group, baseline ARAT score and stratification variables (site and severity of upper limb impairment). A random effect for subject will be included. Secondary outcome measures of MAL, WMFT, FMA, EQ5D-5 L, CSI, and mRS will be analysed using the same approach as used to test the primary outcome, with appropriate distributional families depending on the type of outcome. Pre-specified sub-group analysis: We will conduct sub-group analyses to determine differential effects of the intervention in participants with voluntary finger extension (no extension, partial, or full extension) at 3 months post stroke. The GLMM regression model described above will be fitted within each of the sub-groups. No formal tests of significant interactions will be assessed for these models, since the study is not powered for these tests. The primary analysis will take place when follow-up is complete for all recruited participants. No formal interim analysis is planned.

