### Limitations to the study

In this study protocol, it is acknowledged that in making certain considered choices regarding our research plan, these choices, however well-reasoned, may give rise to other potential limitations, so we would like to note these here. Firstly, we chose to use a broad-based inclusion criteria, in order to make our results applicable to the wider stroke population. So we decided not to exclude people with no finger extension at time of recruitment, neglect/inattention and dyskinesia. The presence of these factors may impede the effects of rehabilitation, but since we were not aware of evidence that task-specific training might not still work with these people, we allowed them to be included. Secondly, for those participants with low baseline scores on the ARAT or no finger extension at the time of recruitment, which would be predictive of poor upper limb recovery, it could be argued that these participants could be closely monitored with more frequent assessments, in order to ascertain whether continuation of therapy is justified. To deal with potential limited recovery of finger extension, in this study we have included two other assessments as well as the ARAT, namely the WMFT and the FMA, which allow improvements to be measured in other movements involving the shoulder, elbow and wrist, even if finger extension has not recovered. However, in planning future studies, it would be good to include a mechanism to justify continuation of therapy. Thirdly, due to finite resources, which were under further pressure due to the effects of Covid, it was not possible to periodically check the fidelity of each individual assessor’s assessment technique, after their initial competence was checked after training. Assessors did receive a thorough training for their role, including supervised assessments with participants. Additional tutorials on the FMA and WMFT were held by zoom as needed, video materials of these assessments being done with patients and scores were provided for extra practice/confirmation and the trainers were made available to assessors for further input when requested. Also, when assessments were returned to the trial manager, they were thoroughly checked and any anomalies followed up. However we acknowledge that periodic checking of assessor technique is desirable in future trials.

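### The trial manager, who randomises participants and receives returned assessments, is admitted to the DMC closed session on unblinded outcome data

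*Protocol article*

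**What the plan says.** The protocol article's Data monitoring section provides for an unblinded report during the trial. The trigger is given as "When the participant number exceeds 50", after which "a report will be provided for the next DMC meeting of the outcome data, unblinded, by the trial statistician". Where such data are discussed there are two sessions, one open and one closed: "with the closed meeting including the DMC, the trial manager, and trial statistician if required (and not the Chief Investigator"). The same section has the DMC address its recommendations to the Chief Investigator and the trial manager.

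Other sections give the trial manager these duties:

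- **Study population:** screens people whom site therapists have identified.
- **Study methods:** "The Trial Manager will randomise each participant using REDCap, then inform the therapist of the treatment allocation and book assessment appointments".
- **Participant recruitment:** telephones participants after randomisation about their next assessment or first therapy visit.
- **Data collection:** the local trial manager takes part in training the outcome assessors.
- **Data management:** the trial manager or a research assistant enters data into REDCap, and the same pair of roles will "recruit the participants, including obtaining consent from those who choose to join the study".
- **Limitations to the study:** "when assessments were returned to the trial manager, they were thoroughly checked and any anomalies followed up".

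**The concern.** A closed session keeps emerging comparative results away from people who run the trial. The article accepts that principle when it excludes the Chief Investigator, but it then admits the role with the most day-to-day contact with participants, treating therapists and outcome assessors. That role also receives the committee's recommendations, so it stands outside the committee whose deliberations it joins.

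What is at stake is operational bias. The primary outcome, the ARAT, is scored item by item on an ordinal scale by an assessor, and assessor blinding is its main protection. Someone who knows both the allocations and the direction of the result could, without intending to, change how they encourage recruitment, speak to assessors, or pursue oddities in completed forms. Once the results have been seen, that knowledge cannot be withdrawn.

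**Working it through.** The plan gives no figure to reproduce. The check sets the sections side by side, with one piece of arithmetic on timing.

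**1. Is attendance stated or inferred?** It is stated. Data monitoring names the trial manager among those in the closed meeting. The condition about being required may attach to the statistician alone or to the trial manager as well. On the first reading the trial manager attends as a rule; on the second, attendance is permitted. Neither reading keeps the role out.

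**2. What does the role already know?** Under Study methods the trial manager carries out randomisation and passes the allocation on, so individual allocations are known before any DMC meeting. What the closed session adds is the aggregate comparison of outcomes between groups.

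**3. Where could the combination act?** The role screens, books assessments, speaks to participants, helps train assessors and receives completed assessments. Two limits apply:

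- The Limitations section speaks of assessments in general and does not say outright who does the checking. That the ARAT is covered, and that the trial manager does the checking, are natural inferences and not stated facts.
- Data collection refers to a local trial manager, and Data management to a trial manager or research assistant at each site, so the duties may be divided among several people. Nothing says that the person in the closed session is one without these duties.

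**4. Is the trial still running at that point?** Inputs: a trigger of more than 50 participants (Data monitoring), a revised expected number of 100 (Modifications due to Covid-19), and a target of 300 (Sample size).

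- Against the revised number: 50 / 100 = 50%.
- Against the original target: 50 / 300 = 16.7%, about 17%.

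These are the earliest points, because the report goes to the next meeting after the trigger. If that meeting is held during recruitment, as the section envisages, then on either figure enrolment and the 6-week and 6-month assessments are still under way.

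**5. Is there a safeguard elsewhere?** Data management says that data entry and changes are logged with comments, which helps in tracing edits afterwards. It does not restrict who learns the comparative result. No section explains or limits the trial manager's presence.

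**The case against.** The strongest counter-argument is that two matters are easily merged. Knowledge of each participant's arm comes from randomising, not from the DMC, and would remain if the trial manager left the closed session. This is correct. Selective querying of forms depends mainly on knowing allocation, so it is treated here as a separate, secondary point.

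The routes of influence also have limits. Clinicians make the first approach, or patients refer themselves. The allocation sequence is computer-generated by a separate unit, so knowing an aggregate difference does not by itself produce selection between arms. Decisions on continuing are not described as the trial manager's alone. These points reduce the likely harm but give no reason for admitting the role to the session.

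A reader might infer four stronger criticisms, which the document does not support:

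- **Contradiction with the blinding statement.** Trial design says "Research personnel responsible for data collection will be blinded to the treatment group to which a participant is assigned". This can be read as meaning the outcome assessors, and the trial manager is not described as scoring any outcome.
- **A hidden interim analysis.** Statistical analysis says "No formal interim analysis is planned". DMC review of unblinded data without a formal analysis is compatible with that, and limits on how the report is used normally belong in a DMC charter, which is not shown.
- **Inflation of the type I error.** Any figure would need an assumed bias in ARAT points. The document gives no basis for one, and such a bias would act through knowledge of allocation and not through the closed session.
- **A data-driven cut from 300 to 100.** The lower number was proposed at the 2020 and 2021 data monitoring meetings and attributed to Covid-19 and slow recruitment. Protocol amendments gives randomised accrual of 12 on 27/08/20 and 31 on 15/09/21, both below the trigger for unblinded data.

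**Conclusion.** The point holds as a defect in a stated rule. It is not an omission that a charter or analysis plan could be presumed to fill, because the article itself fixes who attends. The closed session would give the emerging between-group result to a role that already knows individual allocations and works with participants, therapists and assessors, from about the halfway point of the revised recruitment.

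The size of any bias cannot be computed from the document, and nothing shows that bias has occurred. The conclusion assumes that the attendee holds at least some of the operational duties listed, and that the unblinded report is discussed before recruitment and outcome assessment end. It does not depend on how the condition about being required is read.

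**What to change.** **Main change.** Reword Data monitoring, and the DMC charter to match, so that the closed session consists only of DMC members and the statistician who prepared the unblinded report. The trial manager attends the open session only. If a closed session on unblinded data has already been held, the trial report should state which roles attended.

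**Separate, secondary change.** This arises from Study methods, Data management and Limitations to the study, not from the DMC arrangement. Route queries on outcome forms through existing staff who cannot see allocation. The Data Sciences unit already cleans the data and could do this, but it also creates the randomisation sequence, so the person handling queries must be one without access to it.

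**Cost.** Changes of wording, and a different route for queries using existing staff. The small downside is that operational questions for the trial manager must be raised in the open session.

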### Expected adverse events and safety reporting

There are adverse events that are expected in the stroke population that are not related to the task-specific intervention. These are: death, further stroke, cardiovascular conditions and illnesses relating to old age, and development of secondary complications: such as joint contractures. Poor arm function after stroke is also associated with poor balance and falls. While there is low risk of shoulder pain or hand pain related to the task specific intervention and injury to the hand is not expected as a result of the intervention, musculoskeletal adverse events, in addition to common serious adverse events will be monitored as part of the trial.

In the event of shoulder or hand pain occurring in participants in either group of the trial the clinical physiotherapists or occupational therapists would, as part of their role, expect to treat such symptoms or refer the trial participant to another service. Incidence of expected and unexpected adverse events will be collected by the research physiotherapist/occupational therapist and reported to the Data Monitoring Committee.

### Ethics and dissemination

Ethics review of the protocol for the trial and other trial related essential documents (e.g., Participant Information Statement and consent form) will be carried out by the main Human Research Ethics Committee (HREC), Hunter New England REC, the University of Newcastle Human Ethics Committee, and also site RECs, including Central Coast Local Health District REC, Mid North Coast Local Health District REC, Austin Health REC, La Trobe University HREC, Eastern Health HREC, Western Health HREC.

Any amendments to these documents, will be submitted to the REC for approval prior to implementation. Important protocol modifications will be communicated to the RECs, investigators, sponsor, and Trial Management Committee.

The process for informed consent is as follows. Potential participants will be identified by a clinician, who will check whether potential participants meet the eligibility criteria. If potential participants meet the eligibility criteria, the clinician will make the initial approach to the potential participant and give the person an invitation letter and Patient Information Sheet (PIS; approved by the REC, see Appendix 2). The clinician will ask the person’s permission to pass their contact details onto a member of the research team. The participant will have at least 24–48 h to read the PIS and to discuss their participation with others outside the research team (e.g., relatives or friends) if they wish. The researcher will go through the PIS and explain the project to make sure the person understands the nature and intensity of the interventions, the randomisation procedure and a participant’s right to withdraw at any time without compromising their care and research governance issues. The researcher will answer questions, confirm the participant’s eligibility, and take written informed consent if the participant decides to participate. A model consent form is included at Appendix 3.

### Data protection and participant confidentiality

Data will be collected and retained in accordance with the Australian Code for the Responsible Conduct of Research guidelines (52). Data will be entered onto a purpose designed database and data validation and cleaning will be carried out throughout the trial. Trial data will be entered directly into the study database *via* secure restricted internet access.

All study documentation will be retained in a secure location during the conduct of the study and for 15 years after the end of the study, when all participant identifiable paper records will be destroyed by confidential means. Where trial related information is documented in the medical records, these records will be identified by a label bearing the name and duration of the trial. Australian Good Clinical Practice research guidelines, relevant ‘meta’-data about the trial and the full dataset, but without any participant identifiers other than the unique participant identifier, will be held for up to 15 years on a secure University server. A secure electronic ‘key’ with a unique participant identifier, and key personal identifiers (e.g., name, date of birth and medical record number) will also be held indefinitely, but in a separate file and in a physically different location. These will be retained because of the potential for the raw data to be used subsequently for secondary research.

Data will not be made available for sharing until after publication of the main results of the study. Thereafter, anonymised individual participant data will be made available for secondary research, conditional on assurance from the secondary researcher that the proposed use of the data is compliant with the Australian Good Clinical Practice research guidelines regarding scientific quality, ethical requirements and value for money. A minimum requirement with respect to scientific quality will be a publicly available pre-specified protocol describing the purpose, methods and analysis of the secondary research, e.g., a protocol for a Cochrane systematic review. The second file containing participant identifiers would only be made available for record linkage or a similar purpose, subject to confirmation that the secondary research protocol has been approved by a HREC or other similar, approved ethics review body.

The findings will be disseminated by usual academic channels, i.e., presentation at international meetings, as well as by peer-reviewed publications and through participant organisations and newsletters to participants, where available. No commercially exploitable findings are anticipated.

### Limitations to the study

In this study protocol, it is acknowledged that in making certain considered choices regarding our research plan, these choices, however well-reasoned, may give rise to other potential limitations, so we would like to note these here. Firstly, we chose to use a broad-based inclusion criteria, in order to make our results applicable to the wider stroke population. So we decided not to exclude people with no finger extension at time of recruitment, neglect/inattention and dyskinesia. The presence of these factors may impede the effects of rehabilitation, but since we were not aware of evidence that task-specific training might not still work with these people, we allowed them to be included. Secondly, for those participants with low baseline scores on the ARAT or no finger extension at the time of recruitment, which would be predictive of poor upper limb recovery, it could be argued that these participants could be closely monitored with more frequent assessments, in order to ascertain whether continuation of therapy is justified. To deal with potential limited recovery of finger extension, in this study we have included two other assessments as well as the ARAT, namely the WMFT and the FMA, which allow improvements to be measured in other movements involving the shoulder, elbow and wrist, even if finger extension has not recovered. However, in planning future studies, it would be good to include a mechanism to justify continuation of therapy. Thirdly, due to finite resources, which were under further pressure due to the effects of Covid, it was not possible to periodically check the fidelity of each individual assessor’s assessment technique, after their initial competence was checked after training. Assessors did receive a thorough training for their role, including supervised assessments with participants. Additional tutorials on the FMA and WMFT were held by zoom as needed, video materials of these assessments being done with patients and scores were provided for extra practice/confirmation and the trainers were made available to assessors for further input when requested. Also, when assessments were returned to the trial manager, they were thoroughly checked and any anomalies followed up. However we acknowledge that periodic checking of assessor technique is desirable in future trials.

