### Participant recruitment

Potential participants may be in hospital awaiting discharge or they may already be at home following stroke. In both situations the recruitment procedure will take place over at least two occasions. Screening will take place before consent. First, potential participants will be identified by a clinician, who will check whether potential participants meet the eligibility criteria. If potential participants meet the eligibility criteria, the clinician will make the initial approach to the potential participant, and give the person an invitation letter and Patient Information Sheet (PIS) [approved by the local Research Ethics Committee (REC)]. The clinician will ask the person’s permission to pass their contact details onto a member of the research team. The participant will have at least 24–48 h to read the PIS and to discuss their participation with others outside the research team (e.g., relatives or friends) if they wish. The researcher will go through the PIS and explain the project to make sure the person understands the nature and intensity of the interventions, the randomisation procedure and a participant’s right to withdraw at any time without compromising their care and research governance issues. The researcher will answer questions, confirm the participant’s eligibility and take written informed consent if the participant decides to participate. Those who consent to participate will be assessed at baseline. Following this, participants will be randomised, and the Trial Manager will contact participants by telephone to inform them when their next assessment will be (usual care group) or organise their first therapy appointment and provide the therapist name (task-specific training group). Details of all participants approached for the trial and reason(s) for non-participation (e.g., reason for being ineligible or participant refusal) will be documented.

Strategies being employed for achieving adequate participant enrolment include (a) increasing the number of sites; (b) increased phone and email communication; (c) prompt resolving of local issues relating to recruitment challenges; (d) visiting the sites when possible, and (e) sending a newsletter with news about the trial.

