### Data collection

Data will be collected and stored using a web-based database REDCap, hosted by HMRI on a secure server. After giving consent, a baseline assessment will be conducted for the participant. As well as the outcome measures, demographic data will be collected at baseline including:

Whether thrombolysis or clot retrieval was used (if this information is available)National Institute of Health Stroke Scale (NIHSS)Assessment of upper limb sensory deficit including proprioception (Wrist Position Sense Test (44)) and touch (Tactile Discrimination Test (45))Ability to perform voluntary finger extension (within the Fugl-Meyer Assessment, by test item 25 -‘extend all fingers’)The Montreal Cognitive Assessment (MoCA) (46), a rapid screening instrument for mild cognitive dysfunction. It assesses different cognitive domains: attention and concentration, executive functions, memory, language, visuoconstructional skills, conceptual thinking, calculations, and orientationSelf-efficacy using the Stroke Self-Efficacy Questionnaire (47)Depression using the Hospital Anxiety and Depression Scale (HADS) (48) or the Stroke Aphasic Depression Questionnaire (SADQ) (49). To determine which of these scales is used, language is assessed using the Sheffield Screening test for Language Disorders (receptive language subsection) (50). If the participant scores less than 9 out of 9 on the receptive subsection, the SADQ is administered, instead of the HADSPresence of vascular risk factors, comorbid conditions such as cognitive decline, arthritis and renal disease, other neurological disease, and type of stroke -ischaemic/haemorrhagic, lacunar/large artery/other, cortical/subcortical, whether thrombolytic drugs were used, side of hemiplegia, handedness whether able to walk independently at stroke onset, and whether active hand movement was present at stroke onset.

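### The trial manager knows every participant's arm and also checks, and may enter, the returned outcome forms. This sits badly with the statement that data-collection personnel are blinded.

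*Protocol article*

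**What the plan says.** All places are in the protocol article.

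- **Blinding.** Trial design states: "Research personnel responsible for data collection will be blinded to the treatment group to which a participant is assigned". Study methods puts it more narrowly: "Outcome assessors will be blinded to the treatment group to which a participant is assigned". Outcomes and Data collection also describe the assessors as blinded.
- **Knowledge of the arm.** Study methods: "The Trial Manager will randomise each participant using REDCap, then inform the therapist of the treatment allocation and book assessment appointments". Under Participant recruitment, the trial manager also telephones each participant after randomisation. The content of the call depends on the arm: the next assessment date for usual care, the first therapy appointment and the therapist's name for task-specific training.
- **Handling of completed assessments.** Limitations to the study: "when assessments were returned to the trial manager, they were thoroughly checked and any anomalies followed up".
- **Entry.** Data management: "The Trial Manager/research assistant at each site will enter data into REDCap". That section also says that data entry and changes are logged with comments.
- **What counts as data collection.** The section of that name opens: "Data will be collected and stored using a web-based database REDCap".

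**The concern.** The ARAT is an ordinal scale of 19 items, each scored 0 to 3 by a rater. Therapists know the treatment, and participants are blinded only as far as is practicable. Blind assessment is therefore the main protection of the 6-week comparison.

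That protection can be weakened after the assessor has finished. If someone who knows the arm decides which forms look anomalous and follows them up, queries may be raised more often, or in one direction, in one arm. Any resulting changes would bias the difference between groups.

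The check carries some weight in this trial. Limitations to the study concedes that assessors' technique could not be checked periodically after training, and it offers the trial manager's review as part of the compensation. A log of changes records an edit, but it does not blind the person who prompted it.

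**Working it through.** **Step 1: set the sections side by side.** No figure in the plan decides this point; it turns on who does what.

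| Task | Role | Section | Stated to be blind to arm? |
|---|---|---|---|
| Randomise, pass on allocation | Trial manager | Study methods | No, knows the arm |
| Arm-specific call to participant | Trial manager | Participant recruitment | No, knows the arm |
| Score the ARAT | Outcome assessor | Outcomes; Study methods; Data collection | Yes |
| Receive, check, follow up anomalies | Trial manager | Limitations to the study | Nothing said |
| Enter data into REDCap | Trial manager or research assistant | Data management | Nothing said |

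Trial design promises blinding of personnel responsible for data collection, and the Data collection section covers collection in REDCap. On that reading, a role that enters outcome data and knows the arm does not fit the promise. No section says that scores are locked before the trial manager sees them.

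**Step 2: how large could the effect be?** The documents give no query rate and no direction, so the bias is an assumption.

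- Assumed share of one arm's forms changed: 10% to 20%, all in the same direction.
- Assumed change per form: 3 points (one item moved from 0 to 3, the largest change a single item allows).
- Bias in the mean difference: 0.10 × 3 = 0.3 points to 0.20 × 3 = 0.6 points. Against the 5-point target this is 0.3/5 = 6% to 0.6/5 = 12%.

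**Step 3: standard error of the group difference.** Sample size gives an SD of 18, a baseline to follow-up correlation of 0.72 and 20% loss. The planned total is 300, and Modifications due to Covid-19 gives 100 as the more realistic number.

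- Completers per arm: 150 × 0.8 = 120, or 50 × 0.8 = 40.
- SE = SD × √(1 − r²) × √(2/n), with r² = 0.72² = 0.518.
- n = 40: 18 × √0.482 × √(2/40) = 2.79.
- n = 120: 18 × √0.482 × √(2/120) = 1.61.

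**Step 4: two-sided type I error with that bias.** With d = bias/SE, the error is P(Z > 1.96 − d) + P(Z < −1.96 − d).

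| Randomised | Bias | d | Upper tail | Lower tail | Type I error |
|---|---|---|---|---|---|
| 100 | 0.3 | 0.107 | 3.20% | 1.93% | 5.1% |
| 100 | 0.6 | 0.215 | 4.05% | 1.48% | 5.5% |
| 300 | 0.3 | 0.186 | 3.80% | 1.59% | 5.4% |
| 300 | 0.6 | 0.372 | 5.62% | 0.98% | 6.6% |

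A 1-point bias would give 6.5% and 9.5%. It would need 1/3 of one arm's forms moved by 3 points, which lies outside the assumed range, so it is not used in the conclusion.

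**The case against.** The strongest reply is that there is no firm contradiction. Trial design contrasts data-collection personnel with those who deliver treatment, and elsewhere the same promise is made for outcome assessors only. Data entry sits under a different heading, Data management. On that reading the promise covers assessors, and it is kept. This stands in part: the assessor-blinding statements are not contradicted. The wider sentence in Trial design, read with the REDCap sentence in Data collection, still does not fit the trial manager's tasks.

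Second, the sentence in Limitations to the study says little. It does not name the ARAT, say that the anomalies are scores, or say that the assessor is contacted or a score changed. A missing item or date would fit it as well. This also stands as a limit on the claim. However, the ARAT is the assessment given first priority, and nothing excludes it from the review.

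Third, REDCap user rights and query procedures commonly belong to the data management plan, which is not shown. For that reason the point rests on the roles the article does assign, not on missing detail.

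Two stronger readings are tempting. A reader might infer that the primary scores are unblinded or have been altered. The documents do not support this: the original scoring is blind, and no changed score is reported. A reader might also infer that participants know their treatment, so that assessor blinding is the only safeguard. Trial design and Study methods describe efforts to blind participants. One may doubt how well these work, but the document does not say that participants know.

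**Conclusion.** The point holds as an internal inconsistency and a risk of bias after scoring. One role knows every allocation, reviews all returned assessments and may enter them, while Trial design says that data-collection personnel are blinded and nothing masks the review or the entry.

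The likely effect on the primary test is modest: a shift of 0.3 to 0.6 points, with type I error of about 5.1% to 5.5% at 100 randomised and 5.4% to 6.6% at 300. These figures rest on an assumed query rate, size and direction that no document supplies, and on the plan's own SD, correlation and loss. The inconsistency does not depend on them. The change is worth making because it is cheap and protects the primary endpoint.

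**What to change.** 1. **Forms still to come.** Choose one of two routes for the 6-week and 6-month outcome forms.
   - Have assessors' scores entered and locked before the trial manager sees them.
   - Have checking, querying and entry done by existing staff confirmed to have no access to the allocation. This rules out anyone who holds the sequence, including the Data Sciences staff who created it. The research assistant qualifies only if confirmed to be kept from the allocation, because Data management gives that role several tasks in common with the trial manager.

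   On either route, remove the trial manager's edit and query rights on outcome forms in REDCap. Randomisation and booking stay where they are.
2. **Forms already processed.** Use the existing change log to list every ARAT change made after submission, by arm. If there are any, repeat the primary analysis on the scores as first submitted.
3. **Wording.** Revise Trial design, Data management and Limitations to the study so that they agree on who handles outcome data and whether that person is blind to arm.

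The cost is a change of user rights, a short procedural amendment with existing staff, and slightly slower resolution of queries.
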